**Methods:**

Participants will be healthy individuals across a wide range of ages (6 to 35 years), from two study sites. Participants will undergo pre-exposure and conditioning followed by both a short-term and long-term test of learning, all in a novel virtual reality environment. The unconditioned stimulus will be a brief pressurized puff of air to a maxillary anterior tooth. Pre-exposure dose (low vs. high) and pre-exposure novelty (element stimulus vs. compound stimuli) will be between-subject factors, with stimulus type (pre-exposed to-be conditioned stimulus, a non-pre-exposed conditioned stimulus, and an unpaired control stimulus) and trial as within-subject factors. Pain sensitivity will be measured through self-report and a cold pressor test. It is hypothesized that a larger dose of pre-exposure and compound pre-exposure will potentiate the engagement of the target mechanisms and thereby result in greater latent inhibition in the form of reduced fear learning. Further, it is hypothesized that larger effects will be observed in participants with greater baseline pain sensitivity.

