## Study aim and hypotheses

The aim of the proposed study is to test if a larger pre-exposure dose and compound stimulus presentation potentiates changes in expected relevance and attention to the pre-exposed stimulus, and LI of dental fear. We will also examine whether these effects are larger in individuals with higher level of pain sensitivity.

### Hypothesis 1

A larger dose of pre-exposure, compared to a smaller dose, will (a) increase engagement of the target mechanisms (expected relevance and attention), and (b) strengthen the LI of conditioned fear acquisition, recall, and retention.

### Hypothesis 2

Compared to pre-exposure with only the target stimulus, compound pre-exposure will (a) lead to stronger engagement of the target mechanisms of expected relevance and attention, and (b) strengthen the LI of conditioned fear acquisition, recall, and retention.

### Hypothesis 3

Higher pain sensitivity scores will be associated with increased engagement of the target mechanisms of expected relevance and attention.

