#### Moderator variable measures

*Pain sensitivity* will be assessed with a self-report instrument- the Fear of Pain Questionnaire III [37] in individuals 18 years of age or older and the Fear of Pain Questionnaire, Child report in individuals from 6 to 17 years old [38]. The cold pressor test will be used to provide a behavioral index of pain sensitivity.

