#### Hypothesis

1a: A larger dose of pre-exposure, compared to a smaller dose, will increase engagement of the target mechanisms (expected relevance and attention). Hypothesis 2a: Compared to pre-exposure with only the target stimulus, compound pre-exposure will lead to stronger engagement of the target mechanisms of expected relevance and attention.

For Hypotheses 1a and 2a, changes expected in the candidate mediators should first be observed during the pre-exposure phase. To test these hypotheses during this phase, a two factor repeated measures MANOVA with one-between (pre-exposure group) and one-way within-subjects (trial) factor will be conducted separately for the variables expected relevance and attention. A significant group × trial interaction indicates that mean responses across trials is not the same for each group. If the interaction is present, follow-up analyses will focus on examining the plots of the mean change for each group and testing the degree to which the mean change from first to last trial differs between the groups. For the conditioning phase, a three-way repeated measures MANOVA will be conducted separately for each of the target mechanisms (expected relevance and attention). For these models, pre-exposure groups will serve as the between-subjects factor with stimulus and trial being the within-subject factors, and the analysis model will assess the main effects of each variable, as well as all-two-way and three-way interactions. Follow-up analyses depend on the nature of effects that are present (e.g., type of interactions or main effects). We expect that differences between pre-exposure groups will be greater—particularly at the early trials for stimulus CS^+^ _P_ —than for the other stimulus conditions. As such, follow-up analyses will focus on the degree to which means differ by pre-exposure group and stimulus type for each trial using a Bonferonni-adjusted alpha, as well as examining plots of the mean response by stimulus type and trial for each pre-exposure group.

#### Hypothesis 3

Higher pain sensitivity scores will be associated with increased engagement of the target mechanisms of expected relevance and attention.

To test the third hypothesis, individual differences in pain sensitivity will be included in the above analyses as a moderating variable. This will be done by testing interactions between pre-exposure and pain sensitivity.

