## Discussion

Dental fear is a longstanding issue impacting oral health across the globe [3]. Associative conditioning is implicated as a major etiological factor for excessive dental fear [2], and LI from pre-exposure provides a potential strategy for disrupting dental fear learning. Currently, little is known about the mechanisms responsible for the LI of dental fear. This protocol provides an overview of one study in a series of studies aimed at identifying the mechanisms underlying the LI of dental fear. The primary goal is to assess whether higher pre-exposure dose and stimulus novelty (compound pre-exposure) potentiate the mechanisms of LI proposed in a prominent theoretical model by Hall and Rodríguez [18]. Based on this model, it is anticipated that both factors will engage the theorized mechanisms of expected relevance and attention, and thereby increase the LI of dental fear. To our knowledge, the study will be the first to experimentally assess the impact of compound pre-exposure and pre-exposure dose on the LI of dental fear. Moreover, a strength of this research is the inclusion of a second visit to assess fear recall, as many fear conditioning studies do not provide an extended assessment, which has direct relevance for intervention. Another strength is the inclusion of participants from a wide age range, 6 to 35 years old, which is also uncommon in fear conditioning experiments. This is notable, as age of first dental visits in some cases can extend into adulthood [42]. A final goal of the study is to assess if the mechanisms and indicators of LI of dental fear are associated with individual differences in pain sensitivity.

The results of the present experiment should provide practical information regarding necessary characteristics of future interventions. Specifically, if pre-exposure interventions are devised to diminish dental fear learning, it will be important to know whether such interventions will benefit from higher pre-exposure doses and if compound stimulus presentation will strengthen the effectiveness of an intervention. For example, if a larger pre-exposure dose potentiates LI, dental fear interventions would benefit from long pre-exposure sessions. Ultimately, experiments such as this will provide interventionists the data needed to devise effective strategies to help prevent the likelihood of dental phobia.

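### Hypothesis 3 is worded as an association between pain sensitivity and the mediators, but the only test named for it is a group-by-pain-sensitivity interaction, which does not test that association

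*Protocol article*

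**What the plan says.** In the protocol article, Hypothesis 3 appears in the same words under Study aim and hypotheses and again in the Statistical analysis plan: "Higher pain sensitivity scores will be associated with increased engagement of the target mechanisms of expected relevance and attention". It mentions neither dose nor novelty.

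The Statistical analysis plan then gives pain sensitivity the role of moderator ("individual differences in pain sensitivity will be included in the above analyses as a moderating variable") and names one test: "This will be done by testing interactions between pre-exposure and pain sensitivity". The analyses referred to are the repeated-measures models for the two mediators.

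Elsewhere the article describes two different questions:

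- **Moderation.** The Abstract expects that "larger effects will be observed in participants with greater baseline pain sensitivity". The aim sentence, just before the hypotheses, says: "We will also examine whether these effects are larger in individuals with higher level of pain sensitivity". The Experimental design and Moderator variable measures sections also call pain sensitivity a moderator.
- **Association.** The Discussion says: "A final goal of the study is to assess if the mechanisms and indicators of LI of dental fear are associated with individual differences"; the differences meant are those of pain sensitivity. This covers the indicators of latent inhibition as well as the mechanisms.

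**The concern.** According to the Procedures, every participant receives pre-exposure, of 12 or 24 trials, with a single or a compound stimulus. The Statistical analysis plan combines these conditions into one four-level factor. No group goes without pre-exposure, so an interaction of that factor with pain sensitivity compares slopes among four pre-exposed groups. An association of the kind Hypothesis 3 states would normally appear as a slope shared by all of them, and the interaction removes exactly that shared part.

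Two wrong conclusions are possible. A real and uniform association could be reported as no support for Hypothesis 3. Slopes that differ between groups but average to zero could be reported as support for it. The article also leaves open which of two results is the Hypothesis 3 result, so the choice could be made after both have been seen.

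The Discussion adds a gap in scope. It promises to relate pain sensitivity to the indicators of latent inhibition, but the mediation models described for Hypotheses 1b and 2b contain no pain-sensitivity term.

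**Working it through.** **Inputs from the article.** Total sample size 180 (Participants); one between-subjects factor with four groups (Statistical analysis plan); continuous pain-sensitivity scores (Experimental design). The article says that 180 came from a power analysis but gives no alpha, power, effect size or test, so that figure cannot be reproduced.

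**Assumptions.** Equal allocation, 180 / 4 = 45 per group; two-sided alpha 0.05; one standardised mediator score per participant in place of the full repeated-measures model.

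**Models.** For participant i in group g:

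- M0: y = a_g + e
- M1: y = a_g + b·pain + e (one slope for all groups)
- M2: y = a_g + b_g·pain + e (a separate slope in each group)

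The association in Hypothesis 3 is b ≠ 0, which compares M1 with M0: F on 1 and 180 − 5 = 175 df. The named test is that the b_g are not all equal, which compares M2 with M1: F on 3 and 180 − 8 = 172 df. If all b_g equal b, the null of the second test is true whatever the size of b, so its rejection rate must equal alpha.

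**Common slope** (5,000 simulated trials per row):

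| r | Interaction test rejects | Slope test rejects |
|---|---|---|
| 0 | 4.5% | 4.4% |
| 0.1 | 5.2% | 26.4% |
| 0.2 | 4.9% | 77.1% |
| 0.3 | 5.0% | 98.6% |
| 0.5 | 5.2% | 100% |

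**Check on the slope column** by the noncentral F distribution, with λ = n·r²/(1 − r²):

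- r = 0.1: λ = 180 × 0.01/0.99 = 1.82, power 26.8%
- r = 0.2: λ = 180 × 0.04/0.96 = 7.50, power 77.7%
- r = 0.3: λ = 180 × 0.09/0.91 = 17.80, power 98.7%

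**Reverse case.** With group slopes −0.3, −0.1, 0.1 and 0.3 (mean zero), the interaction test rejects in 68% of runs and the slope test in 5.5%.

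**Intermediate case.** With a slope of 0.3 in one group and zero in the other three, the interaction test rejects in 26% of runs and the slope test in 16%.

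**The case against.** The strongest reply is that the interaction is what the authors meant. The Abstract, the aim sentence, the Experimental design, the heading of the moderator section and the analysis paragraph itself all speak of moderation. On that reading the Hypothesis 3 sentence and one sentence of the Discussion are loosely worded, and the analysis is sound. This stands to the extent that rewording Hypothesis 3 is a full remedy. It does not remove the problem, because the numbered hypothesis is stated twice as an association and the second statement sits directly above a test of something else.

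A second reply is that a moderation model would normally contain the pain-sensitivity main effect, so the association will be estimated anyway. That is likely, but the article does not name that term as the test of Hypothesis 3.

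A third is that the 5% figure holds by construction. It does. It shows which question the test answers and is not evidence about this trial's data.

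Could pre-exposure in the named test mean the contrast between pre-exposed and non-pre-exposed stimuli? The plan for Hypotheses 1b and 2b treats the pre-exposure variable and stimulus type as separate terms, and even that reading gives an interaction and not the stated association.

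A reader might also infer an error from the questionnaire, since the article uses "the Fear of Pain Questionnaire III [37] in individuals 18 years of age or older" and a child form at 6 to 17 years. The document does not support this. It nowhere says that raw scores from the two forms are pooled, and scoring is a detail that an article commonly leaves to the full protocol. The cold pressor test, the second measure, has no age-specific form stated. In simulations of pooled raw scores with no true association (assumed: half the sample children, form offsets of 0.5 to 2 SD, mediator age differences of 0.3 to 0.5 SD), the planned interaction test stayed at 4% to 5%. The false positives, 7% to 64%, arose in the slope test, which the plan does not name.

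**Conclusion.** The concern holds as an internal contradiction: Hypothesis 3 as worded and the test named for it address different questions. At n = 180, under a common slope, the named test has no power beyond alpha, while the slope test has about 0.77 at r = 0.20 and 0.98-0.99 at r = 0.30. The named test can also be significant when the average slope is zero. These figures rest on equal groups of 45, alpha 0.05 and a single mediator score, but the main conclusion does not depend on them, since an interaction test is uninformative about a slope shared by all groups.

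It would go too far to say that the planned analysis is simply wrong, because it fits the moderation question in the Abstract and the aim sentence. The two questionnaire forms are not an error in the plan as written. The mismatch should be settled before analysis, because following the plan as it stands can give a wrong conclusion on Hypothesis 3.

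**What to change.** Choose one of two routes.

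1. **Keep Hypothesis 3 as an association.** Name the pain-sensitivity terms pooled over groups as its test. In the pre-exposure phase this should be pain sensitivity × trial, or its relation to first-to-last change, because the Introduction and the plan for Hypotheses 1a and 2a treat engagement there as change over trials. A slope on the overall level could merely show that more pain-sensitive participants give higher ratings throughout. First-to-last change has the advantage of being defined in the same way for 12 and 24 trials. In the conditioning phase, use the pain-sensitivity slope on the mediators for the pre-exposed conditioned stimulus. Report the group × pain-sensitivity interaction separately, as the moderation test.
2. **Reword Hypothesis 3 as moderation,** keep the interaction as its test, and draw no conclusion about association from it.

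In either case, align the Discussion goal: add matching pain-sensitivity terms to the models for the latent-inhibition outcomes, or remove those outcomes from the goal.

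The cost is a change of wording and, on the first route, reporting terms that a moderation model would normally already contain. The second route may leave little power: in the intermediate case above, 26%.

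If the questionnaire slope is tested, standardising within form and including age group is a sensible safeguard for that new test. Its downside is that it removes real differences in pain sensitivity between children and adults.

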#### Hypothesis

1b: A larger dose of pre-exposure, compared to a smaller dose, will strengthen the LI of conditioned fear acquisition, recall, and retention. Hypothesis 2b: Compared to pre-exposure with only the target stimulus, compound pre-exposure will strengthen the LI of conditioned fear acquisition, recall, and retention.

To assess hypotheses 1b and 2b, mediation analysis will be conducted to estimate direct, indirect, and total effects associated with the pre-exposure groups on the distal outcomes of conditioned fear acquisition, recall, and retention. Figure 1 shows the conceptual model that will be estimated for each distal outcome. In the parallel mediation model shown in Fig. 1, the pre-exposure groups are hypothesized to impact the mediators (expected relevance and attention), which in turn are hypothesized to affect a given fear outcome. Note that there are no within-subjects variables in this path model as the scores for the mediating variables will be obtained from the first trial of the conditioning phase, where stimulus group differences are expected to be strongest, and scores from a given distal outcome will be computed as the average of the scores across specific trials in the recall and then retention phase. Note that if the pre-exposure variable was found to interact with stimulus type in hypotheses 1a or 2a, then this model will be estimated separately for each stimulus type to assess if mediation is present for each stimulus.

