## Methods

### Participants

This is a multisite study, with participants enrolled at universities in south Texas and northwest Ohio. For the United States, the region surrounding the Texas site has a larger than average Hispanic population [30], whereas the region surrounding the Ohio site has a substantial African American population [30]. The sites are therefore expected to provide opportunity to recruit Hispanic and African American participants– populations that are of greater risk for dental anxiety and poor oral health [10, 11].

Community volunteers between the age of 6 and 35 will be recruited using strategies such as a study Facebook page, ads posted in social media, newspapers, email announcements, and flyers at community sites. The sample size of 180 participants was determined by an a priori power analysis. Table 1 provides the inclusion/exclusion eligibility criteria for participation. The study will consist of two in-person visits, scheduled approximately 1 week apart, with participant remuneration of a $50 gift card per visit. The Institutional Review Board of the primary institution approved the research.

**Table 1 Tab1:** Inclusion and exclusion criteria

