### Experimental design

The study will use a mixed design, with two within-subject independent variables and two between-subjects independent variables, and one measured continuous moderator variable. One within-subjects variable is stimulus type [stimulus type: pre-exposed to-be conditioned stimulus (CS^+^ _P_), non-pre-exposed to-be conditioned stimulus (CS^+^ _NP_), and an unpaired control stimulus (CS^−^)]. The second within-subjects variable is time [trial number]. One of the two-level between-subjects independent variables is pre-exposure dose [12 trials vs. 24 trials]. The second two-level between-subjects independent variable is pre-exposure novelty [single stimulus vs. compound stimuli]. Participants will be randomly assigned to one of the four between-subject conditions using the randomization feature in the software Research Electronic Data Capture (REDCap; 31, 32). Randomization will be done in session to obtain allocation concealment [33]. The continuous moderator variables are two individual-difference measures of pain sensitivity.

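### The mediation model described for Hypotheses 1b and 2b names no baseline covariates, so the mediator-to-fear path and every indirect effect are open to confounding

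*Protocol article*

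**What the plan says.** The mediation model is set out in the Statistical analysis plan section of the protocol article, under Hypotheses 1b and 2b: "the pre-exposure groups are hypothesized to impact the mediators (expected relevance and attention), which in turn are hypothesized to affect a given fear outcome". The text goes on to fix a good deal:

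- Mediator scores come from the first conditioning trial.
- Outcomes are averages over certain trials in the recall phase and then the retention phase.
- The model is fitted separately for each stimulus type if group was found to interact with stimulus.
- Estimation is by maximum likelihood in Mplus, with 20,000 percentile bootstrap samples used to test the indirect effects.

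Age, site and pain sensitivity are not mentioned for this model. Fig. 1 is not available in the text reviewed.

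Elsewhere the article describes who these participants are and what is expected of them:

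- Participants: "Community volunteers between the age of 6 and 35 will be recruited", and "This is a multisite study, with participants enrolled at universities in south Texas and northwest Ohio".
- Study aim and hypotheses, Hypothesis 3: "Higher pain sensitivity scores will be associated with increased engagement of the target mechanisms of expected relevance and attention".
- Discussion: a closing goal is to see whether pain sensitivity is associated with the indicators of latent inhibition as well as with its mechanisms.
- Study timeline, Visit 1: the individual-difference measures are completed before randomisation.

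**The concern.** A mediation analysis multiplies two paths. The first, from group to mediator, is protected because group is randomised. The second, from mediator to fear, is an association between two measured variables. Any baseline characteristic that moves both will show up as a mediator effect. Bootstrapping deals with the non-normal distribution of the product; it does nothing about this bias.

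The article supplies one candidate common cause itself. It predicts that pain sensitivity relates to expected relevance and attention, and it plans to relate pain sensitivity to the indicators of latent inhibition. Age is another candidate: one mediator and one fear outcome are both 10-point self-ratings, given by people aged from 6 to 35. Site is a third, since the two regions differ in population and in the languages accepted.

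The way the model is fitted does not remove stable differences between people. No within-person contrast between stimuli is described for the mediator or outcome scores, and fitting the model separately for each stimulus keeps them as levels.

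At stake is the mechanism claim. This model is the only analysis described for Hypotheses 1b and 2b, and a biased second path feeds straight into the conclusion that dose and novelty act through expected relevance and attention.

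**Working it through.** **Inputs from the document.** N = 180 ("The sample size of 180 participants was determined by an a priori power analysis"), four groups, two mediators, one outcome. The derivation of 180 cannot be reproduced, because the article does not give its inputs; that is not held against a condensed article.

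**Assumptions, not in the document.** Four equal groups of 45. One baseline common cause C with standardised effect g on the mediator M and h on the outcome Y, taking g = h. True mediator effect b = 0. The focal group shifts the mediator by a = 0.6 SD. Two-sided alpha 0.05.

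**Step 1: bias in the mediator path.** With M = a·group + g·C + error and Y = h·C + error, each with unit variance within group, the unadjusted coefficient of M is on average g × h:

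- g = h = 0.2: 0.04
- g = h = 0.3: 0.09
- g = h = 0.4: 0.16

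The spurious indirect effect is a × g × h: 0.6 × 0.04 = 0.024, 0.6 × 0.09 = 0.054 and 0.6 × 0.16 = 0.096 SD. The direct effect is wrong by the same amount in the opposite direction, and the total effect is unaffected. If g and h have opposite signs the bias is negative and could hide true mediation.

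**Step 2: false rejection of b = 0.** By the Fisher transformation, with standard error 1/√(180 − 3 − 4) = 1/√173:

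- 0.04: z = 0.53, rejection 8%
- 0.09: z = 1.19, rejection 22%
- 0.16: z = 2.12, rejection 57%

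An indirect effect also needs the first path to be significant. Power for that is about 0.80 (45 against 45 at 0.59 SD, close to the 0.6 assumed). The products are 0.80 × 0.082 = 0.07, 0.80 × 0.221 = 0.18 and 0.80 × 0.565 = 0.45.

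**Step 3: simulation.** 3,000 trials per setting with four groups of 45 and one mediator. Joint significance of the two paths stands in for the percentile bootstrap.

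| g = h | mean b, unadjusted | false indirect effect, unadjusted | false indirect effect, adjusted for C |
|---|---|---|---|
| 0 | 0.00 | 3% | 4% |
| 0.2 | 0.04 | 6% | 4% |
| 0.3 | 0.09 | 19% | 5% |
| 0.4 | 0.16 | 47% | 5% |
| 0.5 | 0.25 | 74% | 4% |

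With adjustment, mean b is 0.00 throughout. A separate simulation used two equal groups, a = 0.5 SD, 2,000 trials and a Monte Carlo percentile interval. It gave 19% at 0.3 and 51% at 0.4 unadjusted, against 5% at both adjusted.

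**Step 4: does a second mediator change this?** Suppose C has effect g on both mediators, which are otherwise independent. The two mediators then correlate at g² and each covaries with Y by gh. Solving b(1 + g²) = gh gives b = gh/(1 + g²): 0.04/1.04 = 0.038, 0.09/1.09 = 0.083 and 0.16/1.16 = 0.138. The bias in each path is slightly smaller, but there are now two indirect effects that can be falsely declared.

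**The case against.** The strongest reply is that this is a condensed article. Covariate lists are often left to a fuller plan, Fig. 1 cannot be seen, and nothing in the text says the model is unadjusted. That stands as a limit: the point concerns the model as described, and a fuller plan may already cover it. But the article describes this model closely, down to the trial from which the mediators are scored and the number of bootstrap samples, and it still names no covariate.

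It is also fair to say that any measured mediator is open to confounding, that Hypothesis 3 is only a hypothesis, and that a common cause at 0.2 does almost no harm.

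A reader might infer more than the document supports:

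- **That the group models also lack pain sensitivity.** They do not. The base models are "a two factor repeated measures MANOVA with one-between (pre-exposure group) and one-way within-subjects (trial) factor" for pre-exposure and, for conditioning, one where "pre-exposure groups will serve as the between-subjects factor with stimulus and trial being the within-subject factors". Hypothesis 3 then adds pain sensitivity to these analyses as a moderator.
- **That every group test loses precision by leaving out age and site.** The factor 1/(1 − R²) gives 1/0.9 = 1.11 to 1/0.7 = 1.43 for assumed R² of 0.1 to 0.3, but it applies to between-person comparisons of level. The group models mainly test interactions with trial and stimulus, from which stable differences in level cancel. Leaving covariates out of a randomised comparison causes no bias in any case.
- **That allocation is unstratified.** The article says only that "Participants will be randomly assigned to one of the four between-subject conditions using the randomization feature". It neither states nor excludes strata, which is ordinary missing detail in an article.

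**Conclusion.** The point holds for the Hypothesis 1b/2b mediation model. As described, that model leaves the mediator-to-fear path, and hence each indirect effect, open to confounding by variables known before randomisation. To say the path is confounded would go too far, because the document reports no association of age, site or pain sensitivity with both the mediators and fear.

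The size depends on those unknown associations. At assumed standardised effects of 0.2 on both sides the false-positive rate is about 6%, which is negligible harm. At 0.3 it is about 19% and at 0.4 about 47-51%, against about 4-5% once the common cause is in the model. These figures rest on a linear model with one mediator, one common cause, no true mediator effect and a group shift of 0.5 to 0.6 SD on the mediator. The total effect of group on fear is not affected.

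**What to change.** Pre-specify age, site and baseline pain sensitivity as covariates in both the mediator equations and the outcome equation in Mplus, including when the model is fitted separately by stimulus. Pain sensitivity should enter as the cold pressor measure and the questionnaire score. The questionnaire changes form at age 18 (Moderator variable measures), so its score should be standardised within the adult and child forms.

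State in the plan that adjustment covers measured common causes only and that unmeasured mediator-outcome confounding remains; a sensitivity analysis for it would be a useful addition.

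Age is needed for eligibility, site is known, and both pain measures are taken before randomisation, so no new data or procedures are needed. The cost is a paragraph of text and four coefficients per equation (age, site, questionnaire, cold pressor) against 180 participants. Fixing the list before the outcome data are analysed also avoids a later choice of covariates.
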